# The impact of *Hafnia alvei* HA4597™ on weight loss and glycaemic control after bariatric surgery — study protocol for a triple-blinded, blocked randomized, 12-month, parallel-group, placebo-controlled clinical trial

**DOI:** 10.1186/s13063-023-07383-0

**Published:** 2023-05-29

**Keywords:** Bariatric surgery, Glycaemic control, *Hafnia alvei* HA4597™, Obesity, Weight loss

## Abstract

**Background:**

Subjects with obesity exhibit changes in gut microbiota composition and function (i.e. dysbiosis) that contribute to metabolic dysfunction, including appetite impairment. Although bariatric surgery is an effective treatment for obesity with a great impact on weight loss, some subjects show weight regain due to increased energy intake after the surgery. This surgery involves gut microbiota changes that promote appetite control, but it seems insufficient to completely restore the obesity-associated dysbiosis — a possible contributor for weight regain. Thus, modulating gut microbiota with probiotics that could improve appetite regulation as a complementary approach to post-operative diet (i.e. *Hafnia alvei* HA4597™), may accentuate post-surgery weight loss and insulin sensitivity.

**Methods:**

This is a protocol of a triple-blinded, blocked-randomized, parallel-group, placebo-controlled clinical trial designed to determine the effect of *Hafnia alvei* HA4597™ supplementation on weight loss and glycaemic control 1 year after bariatric surgery. Patients of Hospital CUF Tejo, Lisbon, that undergo Roux-en-Y gastric bypass are invited to participate in this study. Men and women between 18 and 65 years old, with a BMI ≥ 35 kg/m^2^ and at least one severe obesity-related comorbidity, or with a BMI ≥ 40 kg/m^2^, and who are willing to take 2 capsules of *Hafnia alvei* HA4597™ probiotic supplements (equivalent to 5 × 10^7^ CFU) *vs*. placebo per day for 90 days are included in this study. Assessments are carried out at baseline, 3, 6, 9, and 12 months after the surgery. Loss of weight in excess and glycated haemoglobin are considered primary outcomes. In addition, changes in other metabolic and inflammatory outcomes, gut microbiota composition and metabolites, as well as gastrointestinal quality of life are also being assessed during the trial.

**Discussion:**

The evidence obtained in this study will provide relevant information regarding the profile of the intestinal microbiota of individuals with severe obesity and the identification of the risk/benefit ratio of the use of *Hafnia alvei* HA4597™ as an adjunctive treatment in the maintenance of metabolic and weight control one year after the surgical intervention.

**Trial registration:**

ClinicalTrials.gov NCT05170867. Registered on 28 December 2021.

## Background

Management of obesity stands primarily on achieving an adequate weight loss to reduce its impact on quality of life, morbidity and mortality risk [1, 2]. For patients who are unable to achieve clinically relevant weight loss through therapeutic lifestyle or pharmacological measures, bariatric surgery is considered the most effective intervention for weight loss, prevention of weight regain, and improvement, as well as remission, of many obesity-related comorbidities [3]. Nevertheless, over 20% of all patients do not lose enough weight 1 year after bariatric surgery (< 50% excess body weight) and there is also risk of weight regain after the surgery [4]. Non-adherence to post-surgery dietary recommendations has been reported in 23% of patients, contributing significantly to weight regain [5]. Therefore, identification of new strategies to sustain appetite control to maintain weight loss and metabolic recovery after the surgery is warranted.

It is known that changes in gut microbiota after bariatric surgery play a pivotal role on the beneficial effects related to this surgical intervention, including appetite regulation [6]. In fact, as shown in a clinical study from our group that involved subjects with type 2 diabetes and excess weight [7], gut microbiota changes towards eubiosis preceded glycaemic improvements, demonstrating the important role that the gut microbiome has on metabolic control. Furthermore, previous studies have shown that preoperative gut microbiota composition is a good predictor of bariatric surgery outcomes, including weight loss trajectory [8, 9]. Nonetheless, recent studies indicate that gut microbiota eubiosis is not fully restored after bariatric surgery [6] and that subjects that regained weight have significantly different gut microbiota in comparison to more successful postoperative settings [10]. Hence*,* strengthening the restoration of gut microbiota with probiotics possibly promoting appetite control may be important to improve the metabolic outcomes and weight loss after surgery. Recently, the strain *Hafnia alvei*, a commensal bacterium that belongs to the Hafniaceae family (formerly Enterobacteriaceae), has raised interest regarding its mechanism of action in appetite control [11]. *Hafnia alvei* can synthesize caseinolytic protease B protein (ClpB), which was identified as a conformational antigen mimetic of α-melanocyte-stimulating hormone [11]. ClpB stimulates glucagon-like peptide-1 (GLP-1) and peptide YY secretion by L-cells in the gut and can also stimulate other anorexigenic pathways in the hypothalamus by activating proopiomelanocortin (POMC) neurons [12]. In addition, activation of POMC neurons increases lipolysis and contributes to lowering glucose levels through leptin signalling pathway [11, 13]. Interestingly, gut microbiota of individuals with obesity have low abundance of enterobacterial ClpB [12], which can contribute to appetite dysregulation. Based on these findings, pre-clinical studies were conducted to assess the effect of *Hafnia alvei* as a potential probiotic (*Hafnia alvei* HA4597™) for appetite control and weight management in obese models. Results showed that *Hafnia alvei* HA4597™ supplementation decreased appetite and had anti-obesity and anti-diabetic effects in animal models of obesity [11, 14]. These results were confirmed afterwards in a multicentric, double-blind, randomized, placebo-controlled trial that included 236 overweight subjects, successfully demonstrating the use of *Hafnia alvei* HA4597™ in weight and glycaemic control management [15]. Nevertheless, validation of the effect of *Hafnia alvei* HA4597™ in subjects with obesity is still required, particularly in more severe cases as an adjuvant therapy for bariatric surgery and, possibly, exploring other complementary mechanisms as consequence of gut microbiota modulation, including systemic inflammation and metabolites produced by gut bacteria with relevant metabolic impact. This could contribute to improvement of weight and glycaemic management of subjects with obesity in the long-term and to a better understanding of the role of gut microbiota as therapeutic target in obesity.

## Study objectives

The purpose of this paper is to describe the RESTART project protocol. A study that aims to understand the link between dysbiosis and obesity, assessing the effect of *Hafnia alvei* HA4597™ supplementation as an adjuvant treatment in the context of bariatric surgery for weight loss and glycaemic control. In this regard, the specific aims of this trial are:

Primary aims:To evaluate if *Hafnia alvei* HA4597™ supplementation improves the percentage of excess weight loss.To assess the impact of *Hafnia alvei* HA4597™ supplementation on glycated haemoglobin (HbA1c).

Secondary aims:To evaluate the effect of *Hafnia alvei* HA4597™ supplementation on fasting glucose, HOMA-IR, HOMA-S, HOMA-B, and c-peptide.To analyse the effect of *Hafnia alvei* HA4597™ supplementation on gut microbiota composition.To analyse the effect of HA4597™ supplementation on gut metabolites: ClpB, short-chain fatty acids (acetate, propionate, and butyrate), trimethylamine N-oxide, indole-3-propionic acid, imidazole propionate.To evaluate if *Hafnia alvei* HA4597™ supplementation can improve gastrointestinal quality of life.

## Methods

### Trial design and study setting

This one-year, triple-blinded, blocked-randomized, parallel-group, placebo-controlled clinical trial is designed to determine the effect of *Hafnia alvei* HA4597™ supplementation on weight loss and glycaemic control 1 year after bariatric surgery. The trial is being conducted at Hospital CUF Tejo (Lisboa, Portugal) and samples and data will be analysed at Faculdade de Ciências Médicas, NOVA Medical School, NMS, FCM, Universidade NOVA de Lisboa (Lisboa, Portugal) (NMS, FCM, UNL). The design of the proposed study protocol is shown in Fig. 1.

**Fig. 1 Fig1:**
[figure not shown]
Trial flowchart

#### Recruitment and eligibility criteria

Men and women between 18 and 65 years, with a BMI ≥ 35 kg/m^2^ and at least one severe obesity-related complication, or with BMI ≥ 40 kg/m^2^, that will undergo Roux-en-Y gastric bypass for the first time are informed on the trial and invited to participate. Volunteers are recruited after their first surgery appointment and are given at least 1 week to consider their possible participation. Afterwards, if the volunteer decides to participate and agrees to take a probiotic/placebo supplement twice a day for 90 days, the volunteer is asked to give a written informed consent. Subjects are excluded from the study if one or more of the following conditions are met:Intake of antibiotics and/or probiotics in the previous 12 weeksWeight change > 5% in the previous 12 weeksUnder corticotherapy or under other anti-inflammatory drugsDiagnosis of gastrointestinal disease or other significant illnessPregnancy or breastfeeding

#### Randomization, allocation, and blinding

Eligible participants are randomized using block randomization in a 1:1 ratio to either the probiotic or the placebo group. Blocked randomization is stratified according to HbA1c levels obtained at first visit (baseline), following American Diabetes Association guidelines for pre-diabetes and diabetes diagnosis (normal: < 5.7%; pre-diabetes: 5.7–6.4%; diabetes: ≥ 6.5%) [16]. The randomization is performed using the National Cancer Institute clinical trial randomization tool (https://ctrandomization.cancer.gov/). A minimisation method is used on the allocation process to ensure the required balance across the intervention and control groups. Results are sent to an independent researcher responsible for allocation that is not involved in the recruitment nor in the delivery of the intervention. The allocation is performed right before the beginning of the intervention of each group of randomized participants (in blocks), sending the results to a local researcher in a pre-printed Excel worksheet (Microsoft, Redmond, WA, USA). Randomization and allocation of participants are carried out by different researchers.

The study products are packaged and blinded by an outsourced pharmacy. The package appearance of both products is identical; thus, participants and care providers will be blinded to the intervention. All researchers involved in the trial are also blinded to the intervention allocation until the trial is completed. At the end of the study, researchers performing the statistical analysis will divide the participants into the coded groups and will be unaware regarding the intervention allocation. A member of the research group that is not involved in the study nor participates in the investigation meetings is responsible to keep the sealed envelopes with the allocation of each code in a locked drawer. After performing the analyses, the sealed envelope will be opened by the coordinating and principal investigators.

Unblinding will be needed in case of medical event emergencies or serious medical conditions that may occur during the trial whereby the physician needs to know which treatment they have been receiving. However, given the nature of the intervention and placebo, it is unlikely to occur.

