#### Safety monitoring and compliance

Participants are asked to remark on a daily basis in a paper diary any adverse effects during the intervention. Likewise, the research team also monitors all participants throughout the study (through bi-weekly messages and a call) for any adverse events, in particular gastrointestinal symptoms and possible allergies. In case of serious adverse effects, a thorough follow-up will be conducted to investigate the incident and participants will be advised to stop taking the capsules immediately.

To evaluate compliance, participants register the daily intake of the capsules during the 90 days of intervention and are asked to return all the used and unused bottles with the remaining capsules (if any). It is not specified any concomitant care to be permitted or prohibited.

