### Sample collection and follow-up

Eligible participants are assessed five times during the trial: at baseline (visit 1), 3 months (visit 2), 6 months (visit 3), 9 months (visit 4), and 12 months (visit 5) after bariatric surgery. Intervention (i.e. intake of probiotic or placebo) is administered 3 months after the surgery. All data is collected at Hospital CUF Tejo and the specific assessments carried out at each timepoint are identified in Table 1.

Before each visit, participants are contacted and reminded of their follow-up visits and necessary preparations via e-mails and text messages. Participants are asked to prepare for all the visits by following the instructions:Fasting for 10–12 h (allowed to drink water 4 h before the visit)Having a last meal similar to their usual habitsAvoiding alcohol and caffeine intake on the previous dayAvoiding vigorous physical exercise on the previous day

At baseline, participants respond to a questionnaire to provide sociodemographic characteristics, clinical history, and lifestyle practices. Information regarding changes in medication, supplementation and physical activity are continuously gathered throughout the trial through the electronic patient record.

At all visits, a venous blood sample is collected by a nurse/phlebotomist into sterile serum separator tubes and K_2_EDTA tubes. Subsequently, blood samples are centrifuged at 3000 rpm for 10 min at 4 °C, and aliquoted. For incretin hormones aliquot, DPP-IV inhibitor is added to plasma sample to a final concentration of 10 μL/mL of blood. Participants are also instructed to collect their own faecal samples in sterile tubes with RNAlater, provided by the research team. Subjects describe their stool frequency and consistency of evacuation using the Bristol stool scale [23]. All biological samples are stored at − 20 °C (faecal samples) or − 80 °C (plasma and serum samples) until further analysis.

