Some prespecified subgroup analysis will be done based on some confounding variables such as age, gender, diagnosis of type 2 diabetes, etc., for detecting heterogeneity in intervention efficacy across the strata of mentioned variables. However, these subsamples will be compared to the main dependent variables at baseline. Potential confounding variables will be evaluated in each model. Regression models will be used to predict which factors at baseline most contribute to excess weight loss 1 year after the surgery.

Differences will be considered statistically significant when *p* < 0.05. Effect sizes (Cohen d test) will also be assessed to decide whether a clinically relevant effect is found (|d|> 0.50 indicates a medium effect size and |d|> 0.80 indicates a large effect size).

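### The randomisation strata label HbA1c bands as diabetes status without regard to diagnosis or treatment, so diabetes is only partly balanced between arms and the HbA1c comparison should be adjusted for it

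*Protocol article*

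**What the plan says.** The section Randomization, allocation, and blinding of the protocol article fixes the design: "Eligible participants are randomized using block randomization in a 1:1 ratio", and "Blocked randomization is stratified according to HbA1c levels obtained at first visit (baseline". The cut-points are chosen "following American Diabetes Association guidelines for pre-diabetes and diabetes diagnosis" and are given as "normal: < 5.7%; pre-diabetes: 5.7–6.4%; diabetes: ≥ 6.5" (per cent). The same section adds: "A minimisation method is used on the allocation process to ensure the required balance across the intervention and control groups". It does not name the minimisation factors.

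Four other places bear on this:

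- **Recruitment and eligibility criteria** does not expressly exclude known diabetes or glucose-lowering drugs. Safety monitoring and compliance adds: "It is not specified any concomitant care to be permitted or prohibited".
- **Primary outcomes** counts participants with HbA1c below 5.7% one year after surgery. It makes no reference to medication.
- **Statistical analysis** plans a chi-square test for categorical variables. It lists "diagnosis of type 2 diabetes" among the subgroup factors and says in general terms that possible confounders will be looked at in the models.
- **Sample collection and follow-up** says that at baseline "participants respond to a questionnaire to provide sociodemographic characteristics, clinical history, and lifestyle practices". It adds that medication changes are followed through the electronic record.

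**The concern.** The cut-points are diagnostic thresholds, but some of the people they are applied to may already be diagnosed and treated. Measured HbA1c then reflects the drug as well as the disease. A patient with known type 2 diabetes treated to 6.2% enters the pre-diabetes stratum. One treated to 5.5% enters the normal stratum and already meets the one-year criterion at baseline. In the subgroup analysis both count as having diabetes, so the article works with two definitions and does not connect them.

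Two people in the same band, one treated and one never diabetic, may differ in their chance of HbA1c below 5.7% at one year, since drug treatment may change after surgery. With 58 participants in three strata, a few treated patients falling unevenly could move a count outcome, and the planned chi-square test would not take this into account.

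**Working it through.** The article gives no figure for this point, so there is nothing to reproduce. The classification can be read from the text. The size can only be shown on assumptions.

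**Step 1: where a patient is placed.**

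| Patient (illustrative) | Randomisation stratum | Subgroup by diagnosis |
|---|---|---|
| Known diabetes, HbA1c 5.5% on treatment | normal | diabetes |
| Known diabetes, HbA1c 6.2% on treatment | pre-diabetes | diabetes |
| Known diabetes, HbA1c 6.5% or more | diabetes | diabetes |

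The two classifications part only for people with diabetes below 6.5%.

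**Step 2: how much balance is lost.** From the article: 58 participants, 1:1 allocation, three strata. Assumed: block size 4; diabetes prevalence 30% or 50%; a share m of people with diabetes below 6.5%; everyone below 6.5% split equally over the two lower bands. Each scenario was simulated 20,000 times. D is the between-arm difference in the number of people with diabetes.

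| Strata | 30% prevalence: SD of D; P(abs D ≥ 4) | 50% prevalence: SD of D; P(abs D ≥ 4) |
|---|---|---|
| By diagnosis | 0.9; 0% | 0.9; 0% |
| By HbA1c, m = 20% | 2.0; 8% | 2.4; 14% |
| By HbA1c, m = 40% | 2.6; 18% | 3.0; 25% |
| By HbA1c, m = 60% | 3.1; 25% | 3.4; 31% |
| None | 3.5; 32% | 3.8; 36% |

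With m = 0 the HbA1c strata do as well as strata by diagnosis (SD 0.9, 0%). In every scenario they do better than no stratification.

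**Step 3: a simpler check.** Suppose 8 or 10 of the 58 are treated patients in the lower strata (assumption). With independent 1:1 allocation, the two-sided binomial probability of a 6:2 split or worse among 8 is 2 × P(X ≤ 2) = 0.289. For 7:3 or worse among 10 it is 2 × P(X ≤ 3) = 0.344. These are somewhat high, because blocking holds the arm totals nearly equal. If the lower strata are treated as one pool of 40 split 20:20 (assumption), the hypergeometric values are 0.235 and 0.273. Over pools of 30 to 44 they run from 0.21 to 0.24 and from 0.25 to 0.28.

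**Step 4: effect on the outcome.** A 6:2 or 7:3 split is a difference of 4 people, or 4/29 = 13.8% of an arm. If treated patients differed from the others by 30 percentage points in reaching HbA1c below 5.7% (assumption), the arm difference would shift by 0.138 × 30 = 4.1 points. The standard error of the difference is √(2p(1−p)/29). This is 13.1 points at p = 0.5 and 12.0 points at p = 0.7. The shift is about a third of one standard error.

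**The case against.** The strongest reply is that the article stratifies on HbA1c level and does exactly that. HbA1c is the baseline value of a primary outcome, and the lowest cut-point is the outcome threshold itself, so it is a legitimate stratifier. This stands. A reader might infer from the labels that the randomisation claims to balance diabetes and fails to. The text does not support that: the factor it names is HbA1c level, and the guideline reference explains the cut-points. Nor is diabetes left unbalanced. People at 6.5% or more are balanced directly, and the rest are balanced in expectation.

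A reader might also infer a biased comparison, or take the mean baseline HbA1c of 6.3% in Recruitment status as evidence that treated patients fill the lower strata. Neither follows. The imbalance is random and covered by the error rate of the test. A mean over 14 participants could equally come from a mix of normal and high values.

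Two further replies carry part of the way. The minimisation factors are unnamed, so diabetes could be among them, but this cannot be assumed. A subgroup factor need not match a stratum, and the article does say that confounders will be considered. That sentence, however, does not commit the HbA1c comparison to any adjustment for diabetes, and the test named for categorical variables is unadjusted.

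**Conclusion.** The point holds as a limited one. The stratum labels equate HbA1c bands with diabetes status, treated patients below 6.5% sit in the lower bands, and diabetes diagnosis and treatment are only partly balanced. The subgroup uses a different definition.

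The size is unknown, because neither the prevalence of diabetes nor the share below 6.5% is given. On the assumed ranges, a between-arm difference of four or more people with diabetes arises in 8% to 31% of trials. A difference of four would move the HbA1c result by about 4 points, against a standard error of 12 to 13, if treated patients differ by 30 points. This is a modest chance effect, not a threat to validity. It is worth correcting because the correction costs little, and it assumes that minimisation does not already cover diabetes.

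**What to change.** 1. Keep the strata and call them HbA1c bands.
2. Record for every participant, including those already enrolled, a baseline diabetes class: HbA1c of 6.5% or more, or known type 2 diabetes, or glucose-lowering medication at baseline. Check that the baseline history captures current glucose-lowering drugs.
3. Adjust the one-year HbA1c comparison for HbA1c band and this class. Everyone in the top band belongs to the class, so it adds one parameter and distinguishes people only in the two lower bands.
4. Use the same class for the diabetes subgroup.

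The cost is one derived variable and a few lines of text, fixed before the allocation codes are opened. Some cells will be small, so the model should be kept to these terms. Patient care and sample size do not change.

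Moving known or treated diabetes into the top stratum for participants not yet allocated is optional. It would tighten balance on diabetes but widen the HbA1c range in that stratum, and so loosen balance on the baseline of the outcome. It would also change the rule in mid-trial, so both classifications would have to be kept.

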### Primary outcomes

The primary outcomes are the differences in the number of subjects that will lose at least 50% of excess weight, as well as the number of subjects that will have glycated haemoglobin levels lower than 5.7%, between the probiotic and placebo groups, 1 year after the surgery. The rationale behind the primary outcomes is based on previous studies that have described the effect of *Hafnia alvei* HA4597™. In the preclinical study conducted by Legrand et al. [14], the effect of *Hafnia alvei* HA4597™ supplementation was assessed in two models of obesity, in leptin deficiency *ob/ob* mice and high-fat diet (HFD)-fed obese and overweight mice. Results showed that in both models’ body weight gain was significantly lower by the end of the study (50.1% *ob/ob* and 38.1% HFD), as well as fat gain (38.3% *ob/ob* and 51.9% HFD) [14]. In addition, loss of lean mass was 126.8% lower and food intake reduced 20.8% in the *ob/ob* mice [14]. A second trial was conducted by Lucas et al. [11] using a mice model of obesity characterized by a combination of a HFD-fed obese and a genetic *ob/ob* mice which closely represents the hyperphagia and diet-induced obesity in humans (compulsive eating behaviour combined with hypercaloric diet and functional leptin resistance). The authors observed that *Hafnia alvei* HA4597™ supplementation resulted in 58.1% lower body weight gain, decreased food intake and fat mass gain, and increased lean mass preservation, resulting in an improved lean/fat mass ratio [11]. Moreover, *Hafnia alvei* HA4597™ treatment also improved metabolic outcomes, including glycemia. Basal glucose levels decreased by 1.5-fold compared to standard diet HFD-fed controls [11]. Afterwards, the efficacy of *Hafnia alvei* HA4597™ supplementation was tested in humans [15]. A randomized, placebo-controlled, double-blind trial evaluated the effect of this probiotic (5 × 10^7^ CFU of *Hafnia alvei* HA4597™) on 236 overweight men and women that were following a low-calorie diet [15]. After 12 weeks, significantly more subjects (+ 51%) lost at least 4% of their initial weight comparing to placebo [15]. Furthermore, compared to placebo, subjects in the treatment group had a significant reduction in hip circumference and glycemia, and increased feeling of fullness, which was assessed by a visual analogue scale [15].

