## Statistical analysis

Statistical analysis will be performed using SPSS V.27 (IBM SPSS Statistics for Windows, IBM Corporation, Armonk, NY) and GraphPad Prism V.9 (GraphPad Software, La Jolla, CA, USA).

Participants with low compliance as defined by taking less than 80% of the pills provided by the research team and those lost to follow-up will be excluded from the per-protocol analysis but included in the intention-to-treat analysis. In addition, all participants are strongly advised not to take any probiotic supplements. Participants are asked at each visit about the intake of antibiotics and probiotics supplements, in case of intake in any period of the trial after starting the intervention, participants will also be excluded from the per-protocol analysis but will be included in the intention-to-treat analysis. In case of lost to follow-up, available data from electronic medical records will be collected.

The Kolmogorov–Smirnov test will be used to test the normality of the distribution. Descriptive statistics will be performed, and data will be presented as mean ± standard error of mean (SEM) (for normally distributed continuous variables) or median [interquartile range (IQR)] for nonnormal quantitative data and frequency (percentage) for categorical data. Data will be evaluated for the presence of outliers, violations of normality, and missing data. Major violations of normality will be corrected with an appropriate transformation procedure (i.e. logarithmic transformation for positively skewed and exponential function for negatively skewed data). To analyse the differences in the continuous variables between the intervention and placebo groups, different tests will be used depending on the data distribution. Paired samples *t*-test will be used for normal data and Wilcoxon signed rank test for non-normal data. Categorical variables will be analysed by *X*^2^ test. Correlations between outcomes will be evaluated by Pearson’s chi-square and Spearman correlation test. Relative risks and weighted mean differences will be employed to calculate the dichotomous and continuous data, respectively.

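### Allocation is stratified by baseline HbA1c class, but the named test for the HbA1c primary outcome ignores the strata and so may lose power; the same section also names minimisation without reconciling the two methods

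*Protocol article*

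**What the plan says.** **Allocation.** Under Randomization, allocation, and blinding, the article says: "Eligible participants are randomized using block randomization in a 1:1 ratio to either the probiotic or the placebo group". It continues: "Blocked randomization is stratified according to HbA1c levels obtained at first visit (baseline"), and gives the classes as "normal: < 5.7%; pre-diabetes: 5.7–6.4%; diabetes: ≥ 6.5"%. Two sentences later it says: "A minimisation method is used on the allocation process to ensure the required balance across the intervention and control groups". It does not say which factors are minimised or how minimisation and blocks work together.

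**Outcome.** Under Primary outcomes, the two primary outcomes are counts of responders at one year. One is the number losing at least half of their excess weight. The other is given in these words: "as well as the number of subjects that will have glycated haemoglobin levels lower than 5.7%, between the probiotic and placebo groups".

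**Analysis.** Under Statistical analysis: "Categorical variables will be analysed by *X*^2^ test". For continuous variables: "Paired samples *t*-test will be used for normal data and Wilcoxon signed rank test for non-normal data". Neither sentence contains a stratum term. The following paragraphs plan subgroup analyses, one of them by type 2 diabetes, and say in general terms that possible confounders will be considered in the models. They do not name HbA1c class or link it to the primary comparison.

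**The concern.** Stratified blocks make the arms similar in HbA1c class, so differences between classes contribute little to the observed difference between arms. An unstratified test still counts those differences in its standard error. If class predicts the outcome, the standard error is too large, the test runs below its nominal level, and power is lost.

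The HbA1c responder outcome is where this should matter most, because the lowest stratum boundary and the outcome threshold are both 5.7%. The trial is small (44 evaluable participants planned, 58 recruited), so avoidable loss of power counts.

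The second issue is the allocation method itself. Permuted blocks within strata follow a sequence; minimisation assigns each person in view of those already allocated. The factors to adjust for follow from the method used, and the section leaves a reader unable to tell which that was.

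**Working it through.** **Inputs from the article.** 1:1 allocation; three HbA1c strata; outcome HbA1c below 5.7% at one year; significance at p < 0.05 (two-sided assumed); 44 evaluable, so 22 per arm. The article gives no figure for the power of the HbA1c responder comparison, because its sample size rests on excess weight loss and fasting glucose. There is thus no stated figure to reproduce for this point.

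**Assumptions, not in the article.** Stratum sizes of 8/8/6 per arm (normal / pre-diabetes / diabetes) and response rates by stratum. The only baseline information is a mean HbA1c of 6.3% in 14 participants.

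**Step 1: approximate size of the unstratified test.** With equal numbers per arm in each stratum, the true variance of the arm difference is proportional to W = Σ nₖpₖ(1−pₖ)/22. The chi-square uses T = p̄(1−p̄). The actual type I error is about 2·[1 − Φ(1.96/√(W/T))].

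For 98/80/30%:
- p̄ = (8×0.98 + 8×0.80 + 6×0.30)/22 = 16.04/22 = 0.729, so T = 0.1975.
- W = (8×0.0196 + 8×0.16 + 6×0.21)/22 = 2.697/22 = 0.1226.
- W/T = 0.621 and √ = 0.788, so the effective critical value is 1.96/0.788 = 2.49 and the type I error is about 1.3%.

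The same steps give W/T = 0.1509/0.1983 = 0.761 for 95/75/40% (about 2.5%), and 0.1209/0.1307 = 0.925 for 95/85/70% (about 4.2%).

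**Step 2: simulation with 8/8/6 per arm.** CMH is without continuity correction.

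| Type I error, rates by stratum | Chi-square | CMH |
|---|---|---|
| 98/80/30% | 1.3% | 4.8% |
| 95/75/40% | 2.5% | 4.9% |
| 95/85/70% | 4.4% | 4.8% |

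| Power, placebo vs probiotic | Chi-square | CMH |
|---|---|---|
| 98/70/30 vs 99/95/70% | 38% | 48% |
| 95/60/30 vs 98/88/65% | 34% | 43% |
| 95/85/70 vs 99/97/93% | 25% | 25% |

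**Step 3: a different set-up.** Permuted blocks of 4, stratum shares 35/35/30%, N = 58, odds ratio 5 for power (all assumed).

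| Placebo rates | Type I error, chi-square vs CMH | Power, chi-square vs CMH |
|---|---|---|
| 70/70/70% | 5.0% vs 5.0% | 60% vs 60% |
| 85/70/50% | 3.6% vs 4.6% | 57% vs 59% |
| 95/70/30% | 1.8% vs 4.8% | 46% vs 57% |
| 97/75/10% | 0.4% vs 4.8% | 16% vs 44% |

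**Step 4: continuous outcomes.** N = 44, standardised difference 11.30/14.00 = 0.81, two-sample t-test against a linear model with stratum terms. If strata explain 20/40/60% of the variance (assumed), type I error is 2.7/1.5/0.3% unadjusted against 4.6–5.2% adjusted. Power is 76/79/83% against 83/93/98%.

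**Step 5: attrition.** Starting from 10/10/9 per arm with random 24% loss (1 − 44/58), the chi-square type I error is 2.1% instead of 1.3% at 98/80/30%, and 3.2% instead of 2.5% at 95/75/40%.

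**Step 6: corrected versions.** A continuity-corrected CMH, which approximates an exact test, has type I error of about 1.2–1.6% in the first two null cases of Step 2. Its power in the first two power cases is 30% and 27%, below the plain uncorrected chi-square.

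**The case against.** **Adjustment belongs in the analysis plan.** Adjustment for stratification factors is often left to an analysis plan, which is not shown, and the article does say that confounders will be considered. This stands in part: a later plan may well add the stratum. But the article does more than stay silent. It names an unstratified test for categorical outcomes, and the general sentence neither names the stratum nor attaches it to the primary test. A stratification factor is a design variable known in advance, not a candidate confounder.

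**The size is assumed.** This stands. Response rates after gastric bypass could be flat across classes, and then almost nothing is lost. Attrition also breaks the exact balance and reduces the conservatism. A reader might take the 1.3% figure as the level at which this trial's test will run; the article gives neither the stratum shares nor the rates that would support that.

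**The argument does not reach the weight outcome.** This stands. A reader might infer that the excess-weight-loss comparison suffers equally, but nothing in the article shows that HbA1c class predicts it.

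**The worksheet does not rule out minimisation.** This stands. A reader might infer that minimisation is impossible because allocations come from a pre-printed sheet. The article describes that worksheet as the means of sending results to a local researcher, batch by batch, which is compatible with minimisation. The inconsistency rests only on two methods being named without reconciliation.

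**Conclusion.** The point holds as a loss of efficiency in the HbA1c responder comparison, conditional on HbA1c class being prognostic. That is the natural expectation, since class is the baseline value of the outcome. Under the assumed 8/8/6 split, type I error ranges from about 1.3% (steep gradient) to 4.4% (flat), against about 4.8% for an uncorrected CMH test. The power cost ranges from about 10 points to none. It could be greater under more extreme gradients (27 points at 97/75/10% in Step 3). A reader might take the mismatch as a threat to validity; it is not, because the error is in the conservative direction.

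The allocation description is inconsistent whatever the gradient. The use of paired tests to compare independent arms is a separate matter and is not relied on here.

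**What to change.** 1. Make the primary HbA1c responder analysis stratified by the three HbA1c classes, using CMH without continuity correction or a regression for the responder outcome with stratum terms.
2. Include HbA1c class, or baseline HbA1c, as a covariate in the between-group models for continuous outcomes.
3. Do not default to an exact or continuity-corrected version: with strata this small it can give back the whole gain.
4. In the randomisation section, state the allocation method actually used. If it was minimisation, name its factors and adjust for them.

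The cost is wording in the analysis section and a corrected sentence on allocation, settled before unblinding. No new data or participants are needed.
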